### Sample size

We conducted a power analysis using Monte Carlo data simulation. We conducted the analysis using a mixed effects model with a fixed effect of chemotherapy cycle (time) and random effects for slope and intercept by participants with unstructured correlation [33–36]. Cheng [35] et al. suggest the use of unstructured correlation when time is used as a fixed effect (chemotherapy cycle) and we are not making specific assumptions about the shape of the curve. Due to limited studies of NIRS measurements of patients with cancer, we used the conservative estimate of average recovery kinetics time constant (τ) of patients with chronic heart failure (25.35 seconds) and extrapolate average change in τ throughout chemotherapy from Foulkes using results from Beever [37,38]. We assume that the random intercept will follow a gamma distribution with shape 1.57, a scale of 12.5, and a right shift of 13.25. Additional assumptions from Foulkes [38] and Beever [37] include the random slope is assumed to follow a normal distribution with an extrapolated standard deviation, as well as a normal distribution of the error with standard deviation of 5.54 [39,40]. Analysis indicates that using a linear mixed effects model with sample size of at least n = 30 will be able to detect an effect of chemotherapy on τ with a power of 0.8. Due to potential dropout or missing data, data collection will continue until data is collected on 30 subjects who have completed the study. As the effect of chemotherapy type on τ is unknown and unable to be approximated with data simulation, we are unable to conduct a full power analysis with the effect of chemotherapy type on τ [29,41,42]. Based on treatment regimens of pilot data, chemotherapy type can be divided into cytotoxic (platinum-based, anthracyclines, etc.) for 3–4 cycles and non-cytotoxic such as immunotherapy for an additional 3–4 cycles. In some cases, treatment would be given concurrently and could be treated as a separate group of cytotoxic + non-cytotoxic. We assume that at least n = 8 of each chemotherapy type will be necessary to detect any differences in trajectory of τ over time consisting of 3 or more cycles of chemotherapy Comparisons between drug regimens could be adjusted based on updates to the NCCN guidelines.

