We will analyze the *ΔO*_*2*_*Hb,* Δ*HHb,* and *ΔTSI*, calculated as the change in steady state levels of O_2_Hb, HHb, and TSI respectively from work to rest, with steady state values calculated as the mean value of the final thirty seconds of the stage. For each data set of one on-off kinetics, there will be three work/rest period pairs therefore we will calculate three delta values and average the three delta values to obtain one delta value for O_2_Hb, HHb, and TSI per data set. The three work/rest transitions will allow for reliability testing with intraclass correlation coefficients. For participant data to be included in the final analysis, the participant will need to complete at least three on-off kinetic laboratory visits. Each participant will complete an on-off kinetics at least two weeks apart, but not more than one month apart in accordance with their prescribed chemotherapy treatment regimen. Each on-off kinetics will correspond with the first infusion of a chemotherapy cycle. To allow participants a maximum amount of time to recover from infusions before participating in exercise, the corresponding on-off kinetics takes place within 48 hours of the first infusion of the subsequent chemotherapy cycle. Since chemotherapy treatments vary depending on oncologist recommendation, each participant may complete different lengths of treatment, resulting in each participant having different numbers of data points. This will prevent us from using traditional statistical analysis such as repeated measures ANOVA. Since it is not time itself, but rather the compilation of chemotherapy infusions over time that we predict will cause changes in measures of mitochondrial oxidative function, we will treat the number of chemotherapy cycles as an ordinal variable in this analysis. We will complete an analysis using mixed effects models to predict τ and deltas from the number of chemotherapy treatments with a random intercept for patients. For aim 2, ANOVAs will be used to assess differences in mitochondrial capacity between drug regimens at each chemotherapy cycle.

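### Aim 1 was powered with a random slope over cycles but is to be analysed with a random intercept alone, so the stated 0.8 power does not describe the planned analysis

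*Protocol article*

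**What the plan says.** Two sections of the protocol article each fix a mixed model for the change in τ over chemotherapy cycles.

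- **Sample size.** The Monte Carlo power analysis uses a fixed effect of cycle and "random effects for slope and intercept by participants with unstructured correlation". Slopes are taken to differ between patients: the "random slope is assumed to follow a normal distribution with an extrapolated standard deviation". The residual SD is 5.54. The conclusion is that a "sample size of at least n = 30 will be able to detect an effect of chemotherapy on τ with a power of 0.8".
- **Data analysis and statistical analysis.** The plan is to fit "mixed effects models to predict τ and deltas from the number of chemotherapy treatments with a random intercept for patients". On coding it says "we will treat the number of chemotherapy cycles as an ordinal variable in this analysis". No random slope is named.

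The Sample size section gives no number for the mean slope (it says only that the authors "extrapolate average change in τ throughout chemotherapy"), the slope SD, alpha or the number of visits simulated.

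**The concern.** A random-intercept model has no term for patients whose τ rises faster or slower than average. It counts that variation as independent visit-to-visit error. Slope differences build up systematically over visits within a patient, so the precision of the average trend is then overstated, and more so the more visits each patient has. A power figure simulated with the slope term does not carry over to an analysis without it.

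Aim 1 is the only aim with a power calculation; the protocol says that a full one for chemotherapy type was not possible. At stake are the p-value and confidence interval for the main longitudinal result.

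**Working it through.** **The plan's own figure.** The 0.8 can be neither reproduced nor refuted, because mean slope, slope SD, alpha and visit count are missing. The check is therefore conditional: set the mean slope so that the random-slope trend test has power 0.80, then see what the random-intercept analysis does with the same data.

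**Inputs from the protocol.** n = 30; residual SD σ = 5.54, so σ² = 30.69.

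**Inputs assumed.** Two-sided alpha 0.05; slope SD s = 1 or 2 s per cycle; K equally spaced visits, K = 3, 4, 5, 7 or 9. Three is the minimum for inclusion. Counting one baseline test plus one per cycle, 3-4 cycles give 4-5 visits, and 3-4 plus 3-4 cycles give 7-9.

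**Formulas (balanced data).** Sxx = K(K² − 1)/12 is the spread of the cycle numbers.

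- True variance of the estimated mean slope: (σ²/Sxx + s²)/n.
- Variance that the random-intercept model reports, on average: (σ²/Sxx + s²/(K − 1))/n.
- SE ratio r = square root of the second over the first.
- Approximate type I error = 2 × [1 − Φ(1.96 r)].

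**Example, K = 7, s = 1.** Sxx = 28 and σ²/Sxx = 1.096. True: 1.096 + 1 = 2.096. Reported: 1.096 + 1/6 = 1.263. r = √(1.263/2.096) = 0.776. 1.96 × 0.776 = 1.521, which gives a type I error of 12.8%.

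**All settings.** The last two columns are simulated with 20,000 replicates per setting. Each cell gives s = 1, then s = 2.

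| Visits | SE ratio r | Type I, formula | Type I, simulated | Joint ordinal test, power |
|---|---|---|---|---|
| 3 | 0.985, 0.947 | 5.4%, 6.4% | 5.3%, 6.3% | 0.72, 0.75 |
| 4 | 0.952, 0.858 | 6.2%, 9.3% | 6.0%, 8.9% | 0.69, 0.76 |
| 5 | 0.903, 0.759 | 7.7%, 13.7% | 7.7%, 13.8% | 0.69, 0.79 |
| 7 | 0.776, 0.588 | 12.8%, 24.9% | 13.3%, 25.1% | 0.73, 0.85 |
| 9 | 0.649, 0.474 | 20.3%, 35.3% | 20.4%, 35.8% | 0.79, 0.89 |

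- The type I columns are for a random-intercept model with numeric cycle. The linear contrast of an ordinal cycle factor gave the same figures to within 0.4 percentage points, so ordinal coding does not repair the standard error.
- The random-slope analysis of the same data had type I error 4.8-5.2% and, by calibration, power 0.80.
- At the calibrated slope, the random-intercept trend test rejects in 82-98% of data sets. The excess over 80% comes from the short standard error and is not real power.
- The joint test over all cycles (K − 1 degrees of freedom) has type I error of 5-6% with 3-5 visits, 6-8% with 7 and 7-11% with 9.

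**Check with fitted mixed models.** With unbalanced data (4-7 visits, the protocol's gamma intercepts, 300 null data sets per setting), the random-intercept model rejected in 12% (s = 1) and 23% (s = 2). With a random slope it rejected in 2% and 5%.

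**The case against.** The best reply concerns size. No slope SD is stated, and with few visits the effect is small: 5-6% at 3 visits and 6-9% at 4. Few visits is a fair reading. Sessions of up to 60 minutes within a 300-minute total give five full-length sessions, one of them the lactate threshold test, which leaves four on-off tests. Shorter sessions would allow more, and the Sample size section's additional 3-4 cycles point that way, so 7-9 visits are possible but not established. This limits the size and leaves the contradiction in place.

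A second reply is that ordinal coding is deliberate, since the Sample size section disclaims assumptions about the shape of the curve. That stands. Ordinal coding is not an error, and the wording does not show that the simulation tested a numeric one-degree-of-freedom trend.

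A reader might go further and infer that the study is underpowered. The documents do not support that. No joint test is specified; an ordinal factor can be tested by a linear contrast; and at slope SD 2 with 7 or 9 visits the joint test exceeds 0.80, though with a raised error rate. Joint-test power near 0.5 arises only with many visits and a slope SD of zero, which contradicts the plan's own assumption that slopes vary. Nor can the 20-36% error rates be read as the expected result; they are the top of an assumed range.

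Finally, this is an observational pilot. That lowers the stakes, but the article still claims a power of 0.8.

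**Conclusion.** The two sections specify different random-effects structures for the same aim, and nothing reconciles them. Given the plan's own assumption that slopes vary, the random-intercept standard error for the cycle trend is too small, and the stated power does not belong to the planned analysis. The direction is certain for a trend test. The size is not: the type I error runs from barely above 5% to about 36% over 3-9 visits and a slope SD of 1-2 s per cycle, at an assumed two-sided 0.05. If cycle is tested jointly, the consequence is a power of about 0.69-0.89 in place of 0.80, and below 0.80 in seven of the eight settings with 3-7 visits. The documents do not say which test will be used.

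**What to change.** 1. In the analysis section, add a by-patient random slope for cycle number, with unstructured covariance with the intercept, to the aim 1 model. This matches the Sample size section and is compatible with ordinal coding of the fixed effect.
2. State that, if this model does not converge, patient-clustered small-sample robust standard errors are used in place of the intercept-only ones.
3. Name the cycle test before analysis: linear slope or contrast, or joint test over cycles. Either is defensible.
4. Restate the power for that test, giving alpha, mean slope, slope SD and number of visits.

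Rerunning the simulation under the random-intercept analysis would align the two sections, but would not correct the standard error if slopes vary.

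The cost is a sentence or two of wording, one line of model code and one rerun of the simulation. Confidence intervals widen by a factor of about 1/r: 1.05 with 4 visits and slope SD 1 (1/0.952), and more where slopes vary more or visits are more numerous, which is uncertainty that the present model hides. With 26 participants already through the protocol of the planned 30, the sample can hardly be redesigned, but the model can still be fixed before analysis.

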Assessment of mitochondrial capacity with NIRS includes studies of clinical populations with peripheral artery [27], chronic kidney [24], and neurologic diseases such as traumatic spinal cord injury and multiple [22], as well as comparisons with healthy [28] and age-related differences in skeletal muscle oxidative [17]. However, there is a dearth of NIRS studies examining the effects of chemotherapy on skeletal muscle mitochondrial function in patients with cancer. Only two studies to our knowledge have utilized NIRS to measure muscle oxygenation variables in cancer survivors. Ederer, et al. [29] determined that [HHb] and [Hb]total were significantly lower in eight cancer survivors (all eight received chemotherapy and five received radiation) compared to healthy controls during exercise at ventilatory threshold. Grigoriadis et al. [30], did not find a significant difference in muscle oxygenation variables between 23 patients with breast cancer (16 received chemotherapy, nineteen received radiation therapy, and 21 received hormonal therapy) and 23 participants who served as age and BMI matched controls. Recent literature of near infrared spectroscopy related to cancer primarily involves detection and identification of cancerous [31] or the use of near infrared light as a photoimmunotherapy [32]. Therefore, the hypothesized loss of mitochondrial capacity throughout chemotherapy treatment has not been studied longitudinally starting at baseline and tracking through the chemotherapy regimen in breast and gynecologic cancer patients with NIRS to date.

The aims of our study are to develop a protocol that 1) assesses mitochondrial dysfunction in cancer patients using exercise that is tolerable for the patients throughout the entire chemotherapy regimen and 2) observe the changes in mitochondrial functional capacity between different chemotherapy regimens for each chemotherapy cycle. The protocol also will help us evaluate a potential correlation between subjective self-reported fatigue and perceived effort with corresponding objective whole-body metabolic measurements and NIRS measurements. The proposed study will help inform clinical decision makers in the oncology community regarding current chemotherapy regimens (based upon the National Comprehensive Cancer Network, NCCN) that patients may best tolerate for cachexia and fatigue.

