### Experimental design

We will use an observational mixed model repeated measures design to longitudinally compare (pre-chemotherapy and throughout treatment) patients’ skeletal muscle mitochondrial capacity of the vastus lateralis during stationary cycling. ANOVAs will be used to assess this same mitochondrial capacity between chemotherapy regimens at each chemotherapy cycle. Pearson or spearman correlations will be used to assess relationships between self-reported fatigue and effort values and metabolic measurements (whole-body as well as NIRS). The study population will include female patients with breast or gynecological cancer. All testing will take place in the University of South Carolina School of Medicine Greenville’s Human Performance Laboratory in the Prisma Health Cancer Institute.

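### Aim 2 is analysed by separate ANOVAs of levels at each cycle, which ignore the baseline visit and cannot test the change or trajectory differences that the plan is about

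*Protocol article*

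**What the plan says.** The aim 2 analysis is fixed twice. The Experimental design section says that "ANOVAs will be used to assess this same mitochondrial capacity between chemotherapy regimens at each chemotherapy cycle", and the section Data analysis and statistical analysis repeats that "For aim 2, ANOVAs will be used to assess differences in mitochondrial capacity between drug regimens at each chemotherapy cycle". Neither mentions baseline.

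The mixed model in the data analysis section predicts τ and the deltas from the number of treatments, with a random intercept per patient. It has no regimen term and no regimen-by-cycle term. The deltas are work-to-rest differences within one visit, so they are not changes from the pre-chemotherapy visit.

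Two other sections describe a different target. The Introduction words aim 2 as to "observe the changes in mitochondrial functional capacity between different chemotherapy regimens for each chemotherapy cycle". The Sample size section assumes that "at least n = 8 of each chemotherapy type will be necessary to detect any differences in trajectory of τ over time", after stating that "we are unable to conduct a full power analysis with the effect of chemotherapy type on τ". It also describes patients who receive cytotoxic treatment for 3–4 cycles and then "non-cytotoxic such as immunotherapy for an additional 3–4 cycles".

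**The concern.** An ANOVA at one cycle asks whether mean τ differs between regimen groups at that cycle. It does not ask whether τ has moved differently since baseline. The oncologist chooses the regimen, so groups may differ before the first infusion. Such a difference carries into every later cycle and looks like an effect of the drugs.

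The plan also assumes a wide spread of τ between patients, and a comparison of levels leaves all of it in the error term. The tests are repeated at every cycle, with no single test that decides aim 2.

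The article says that results will help inform decision makers about which regimens patients tolerate best, so a spurious or missed regimen difference would matter. The pre-chemotherapy test is a condition of staying in the study, so the data needed for a better analysis are already collected.

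**Working it through.** **Inputs (Sample size section).** "random intercept will follow a gamma distribution with shape 1.57, a scale of 12.5, and a right shift of 13.25"; error SD 5.54 s; stated mean τ 25.35 s; 8 patients per type. No number is given for the random-slope SD or for the type effect. I assume two-sided 0.05, 80% power, slopes independent of intercepts, and a slope SD of 0 to 3 s per cycle.

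**The plan's figure.** The n = 8 cannot be reproduced: it is an assumption without effect size, alpha or power. The check therefore asks what 8 per group can detect.

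**Spread of τ at one visit.**
- Intercept SD = √1.57 × 12.5 = 15.66 s.
- Single-visit SD = √(15.66² + 5.54²) = 16.61 s.
- Share between patients = 15.66² / 16.61² = 0.89.
- The gamma's mean is 13.25 + 1.57 × 12.5 = 32.9 s, not 25.35 s. A scale of (25.35 − 13.25) / 1.57 = 7.71 restores the stated mean. The intercept SD is then 9.66 s and the single-visit SD 11.13 s. Both versions are carried below.

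**Detectable difference, 8 versus 8.** The noncentral t distribution with 14 degrees of freedom gives a standardised difference of 1.507.
- Per-cycle ANOVA: 1.507 × √(σb² + σe² + k²σs²), where σb is the intercept SD, σe the error SD, σs the slope SD and k the cycle.
- Baseline as covariate: 1.507 × √(σb² + σe² + k²σs² − σb⁴/(σb² + σe²)), ignoring the one degree of freedom spent.

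| Gamma | Slope SD, cycle | ANOVA of levels | Baseline as covariate | Variance ratio |
|---|---|---|---|---|
| as stated | 0, any | 25.0 s | 11.5 s | 4.8 |
| as stated | 1, cycle 4 | 25.7 s | 13.0 s | 3.9 |
| as stated | 3, cycle 4 | 30.9 s | 21.4 s | 2.1 |
| rescaled | 0, any | 16.8 s | 11.0 s | 2.3 |
| rescaled | 3, cycle 4 | 24.7 s | 21.2 s | 1.4 |

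With slope SD 0, a simple change from baseline has SD 5.54 × √2 = 7.83 s and detects 11.8 s under either gamma. Against mean τ, the ANOVA's detectable difference at slope SD 0 is 25.0 / 25.35 = 99% of the stated mean, 25.0 / 32.9 = 76% of the mean that the gamma implies, or 16.8 / 25.35 = 66% after rescaling.

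**Repeated testing.** I simulated three groups of 8 with no regimen effect, slope SD 0 and an unadjusted 0.05 test at each cycle, with 20,000 runs per setting. The chance of at least one false positive over 3 to 8 cycles is 9 to 13% with the stated gamma and 11 to 19% with the rescaled one. This is for one outcome. The plan has six: τ and delta for each of O2Hb, HHb and TSI.

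**Type and cycle.** A patient treated sequentially is in the cytotoxic phase at early cycles and the non-cytotoxic phase at later ones. If regimen is coded as cytotoxic versus non-cytotoxic, such patients mostly fall in the same category at any one cycle. The contrast then has little support within a cycle, and across cycles it is tied to cycle number.

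**The case against.** The plan does not claim that 8 per type gives adequate power. It says that the type effect is unknown, that no full power analysis was possible, and that 8 is an assumed minimum. A reader might infer that the n = 8 is a failed calculation, and the text does not support that. What stands is that the figure is unsupported and refers to trajectories, which the stated analysis does not test.

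The Introduction asks for a comparison at each cycle, so a per-cycle analysis partly fits. It asks for changes, however, and an ANOVA of levels does not deliver them.

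The gain from using baseline depends on an undisclosed slope SD. A reader might quote only the 4.8-fold saving, but that needs slope SD 0 and the stated gamma. At cycle 4 the range is 2.1 to 4.8, or 1.4 to 2.3 after rescaling. This objection stands, and it is why ranges are given.

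The false-positive rate is modest for a pilot, and an analysis plan that is not shown may deal with multiplicity. The upper end may also not be reached: 300 minutes in sessions of 60 minutes allows 300 / 60 = 5 sessions, which is the lactate test, the baseline and three on-treatment visits. Shorter sessions would allow more.

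A reader might also infer that regimen is confounded with cycle throughout aim 2. That arises only under the cytotoxic versus non-cytotoxic coding. Patients on different cytotoxic regimens at the same cycle remain comparable in this respect.

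**Conclusion.** The concern holds. The stated aim 2 analysis compares levels between non-randomised groups, ignores a baseline visit that the study already collects, and cannot test the change or trajectory differences named elsewhere in the article. With 8 per group it detects about 25 s at one cycle (16.8 s rescaled), against 11 to 12 s with baseline used at slope SD 0. At slope SD 3 and cycle 4 the comparison is about 31 s against 21 s (25 s against 21 s rescaled). These figures assume two-sided 0.05, 80% power and slopes independent of intercepts.

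Even the better analysis sees only large differences, so aim 2 is exploratory either way. A reader might grade this as a fault that invalidates the trial. The documents do not support that: this is a pilot, the n = 30 is justified for the overall effect of chemotherapy, and the regimen comparison is openly unpowered. Nor do these points call for a tumour-site covariate, since the eligibility section gives reasons for modelling the two cancer groups together. The change should be made, but it is not a condition for the rest of the study to stand.

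**What to change.** 1. Replace the per-cycle ANOVAs with one mixed model that includes the baseline visit as the first observation and has a single overall regimen-by-cycle test. Keep cycle categorical or ordinal, as the data analysis section has it, or state a linear trend as an assumption.
2. If a smaller change is preferred, keep the per-cycle comparisons and add baseline τ as a covariate. This removes most of the between-patient spread, but it leaves the repeated testing in place and gives no overall trajectory test.
3. Where type switches within a patient, code it as time-varying.
4. Label aim 2 exploratory. Restate the n = 8 sentence as an unpowered assumption, with the difference that 8 per group could detect over a range of slope SDs.
5. Date and document the change before any regimen comparison is run. The Trial status section reports that 26 participants have completed.

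The cost is wording and analysis code, with no new data. A linear trend, if used, adds an assumption about the shape of the curve, and the aim 2 claim becomes more modest.
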